**Methods/design:**

The study is a one year 1:1 cluster randomized controlled trial of the MOVEdiabetes programme (intervention) versus usual care in eight primary health care centres in Oman. The MOVEdiabetes programme utilizes face to face physical activity consultations promoting 150 min of moderate to vigorous physical activity per week (≥600MET-mins/week), pedometers to self-monitor step counts and monthly telephone WhatsApp messages for follow up support. Inactive adults with type 2 diabetes and no contraindication to physical activity will be recruited over a two months period, and followed up for 12 months. To demonstrate a 50% between group difference in physical activity levels (MET-mins/week) over 12 months, (at a power of 80%, and significance level of 5%), 128 participants would be required to complete the study (64 in each arm). Based on a drop-out rate of 20%, 154 participants would require to be recruited (77 in each arm). Assuming a recruitment rate of 70%, 220 potential eligible participants would need to be approached. The primary outcome is change in levels of physical activity measured by the Global Physical Activity Questionnaire. In addition, accelerometers will be used in a sub group to objectively assess physical activity. Secondary outcomes include changes in metabolic and cardiovascular biomarkers, change in self-reported health, social support, self-efficacy for physical activity, and perceived acceptability of the program. All intervention delivery and support costs will be monitored.

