## Study design/location/recruitment

### Randomisation

The study is a 1 year 1:1 cluster randomized controlled trial of the MOVEdiabetes intervention versus usual care. A cluster randomization design was used to minimize between group contamination by having the two groups (intervention and comparison) from independent health centres. Group allocation will be generated using a random numbers table generated in SPSS v21 by an independent statistician in Oman Ministry of Health. All health centres (8) will be randomised to deliver either the intervention (*n* = 4) or usual care (*n* = 4). Health centres will be informed of their allocation verbally by the project investigator and will receive an envelope containing invitation letter and project materials.

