## Measures/assessment instruments

Baseline and follow-up data will be collected face to face and from the electronic health information system in the health centre (AlShifa system) (Table 1).

**Table 1 Tab1:** Outcome measures

	Tool	When	
		Intervention	Comparison
Primary outcome			
GPAQ-MET-mins/week	Questionnaire	B, 3 F, 12 F	B, 3 F, 12 F
Accelerometer (activePAL^TM^)	Reporting step count, MET-min/week, and sitting time	B, 3 F, 12 F	B, 3 F, 12 F
Pedometer (YAMAX Digi-walker SW-200)	Reporting step counts	B, 3 F, 12 F	-
Secondary outcomes			
Socio-demographic data	Questionnaire	B	B
Height (m)	Stadiometer	B	B
Body weight (Kg)	Calibrated scales	B, 3 F, 12 F	B, 3 F, 12 F
Waist circumference (cm)	Tape measure	B, 3 F, 12 F	B, 3 F, 12 F
Lipid profile (mmol/l)	Blood test (venous fasted sample)	B, 3 F, 12 F	B, 3 F, 12 F
Blood pressure (mmHg)	Sphygmomanometer	B, 3 F, 12 F	B, 3 F, 12 F
^a^HbA1c (%)	Blood test (fasted sample)	B, 3 F, 12 F	B, 3 F, 12 F
Self-assessed general health	Questionnaire	B, 3 F, 12 F	B, 3 F, 12 F
Self-efficacy for PA	Questionnaire	B, 3 F, 12 F	B, 3 F, 12 F
Social support for exercise	Questionnaire	B, 3 F, 12 F	B, 3 F, 12 F
Cost analysis (description)	Detailed cost description	12 F	-
Exit survey	Questionnaire (participants and project officers)	12 F	-

(B = baseline; 3 F = 3 month follow-up, 12 F = 12 month follow-up)

^a^while blood collection for HbA1c at 12 month is mandatory, it is only done at baseline and 3 month if missing from the electronic health information system or recorded within more than 4 months prior to the measurement visits

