## Statistical analysis

The initial quantitative analysis will be an intention-to-treat analysis between the two cluster groups (intervention versus control) but secondary analyses will explore the effect of actual treatment received. The initial analysis will involve standard two-sample comparisons (parametric or nonparametric as dictated by the distribution of the data) looking at effect sizes at 3 and 12 months using t-tests or Mann-Whitney tests for differences in means as well as repeated measures or chi squared tests for differences in proportions. Differences by health centre will be explored and, if statistically significant will be entered in a mixed model as a random effect. The balance of characteristics between treatment and control arms will be tabulated and if differences are noted, adjustment will be made for these in linear regression models.

Results from the open-ended questions in the exit survey will be analysed thematically to identify the perceived acceptability of the intervention (content, delivery and aims) to the participants and project officers (health care providers).

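### Covariates are adjusted for only where arm differences are noticed, so baseline activity may go unadjusted at a cost in precision and conditional bias

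*Protocol article*

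**What the plan says.** All references are to the protocol article.

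- **Outcome.** The abstract (Methods/design) states: "The primary outcome is change in levels of physical activity measured by the Global Physical Activity Questionnaire". Table 1 lists "GPAQ-MET-mins/week" at baseline, 3 months and 12 months in both arms.
- **First analysis.** Under Statistical analysis: "The initial analysis will involve standard two-sample comparisons (parametric or nonparametric as dictated by the distribution of the data"; it continues "looking at effect sizes at 3 and 12 months using t-tests or Mann-Whitney tests for differences in means". These tests carry no covariates.
- **Covariates.** The same section says: "The balance of characteristics between treatment and control arms will be tabulated", and then "if differences are noted, adjustment will be made for these in linear regression models". It names no covariate and sets no threshold.
- **Centre.** Health centre enters a mixed model as a random effect, but only if differences between centres are statistically significant.
- **Design.** Under Randomisation: "All health centres (8) will be randomised to deliver either the intervention" or usual care, four centres to each.

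**The concern.** The rule lets the observed arm differences decide which covariates enter the model, and it leaves open what counts as a difference. Two analysts with the same data could fit different models and both comply with the text.

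Baseline activity is likely to be among the best predictors of later activity, and every participant supplies it. Leaving it out unless an imbalance is seen has two costs:

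- **Precision.** The variance that baseline explains stays in the error term, even when the arms are balanced.
- **Conditional bias.** Randomisation makes the comparison unbiased on average. Given a particular baseline gap, a follow-up comparison is pulled in the direction of the gap and a change-score comparison in the opposite direction. Only adjustment by regression removes both shifts.

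With four centres per arm, such gaps are more frequent than in an individually randomised trial of the same size.

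**Working it through.** **Inputs from the article.** 64 completers per arm, 80% power, 5% significance, 8 centres; 128/8 = 16 completers per centre.

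**Assumptions (not in the article).** Two-sided test; the stated 50% difference acts as 0.5 SD; equal baseline and follow-up variance; correlation r between baseline and follow-up; ICC of 0 or 0.05.

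**1. The plan's own figure.** n per arm = 2(1.960 + 0.842)²/0.5² = 62.8, so 63 by the normal approximation. By the noncentral t, power is 0.795 at 63 and 0.801 at 64. The stated 64 per arm reproduces, so 0.5 SD is a reasonable yardstick below.

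**2. Variance of the treatment contrast, in units of the follow-up variance.** Follow-up value: 1. Change score: 2(1−r). Baseline as covariate: 1−r².

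- Adjusted against change score: (1−r²)/[2(1−r)] = (1+r)/2. At r = 0.3 this is 0.65 (35% less); at r = 0.6 it is 0.80 (20% less).
- Adjusted against follow-up value: 1−r². At r = 0.3 this is 0.91 (9% less); at r = 0.6 it is 0.64 (36% less).

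**3. Largest gap left unadjusted if a difference means p<0.05.** t(0.975, 126) × √(2/64) = 1.979 × 0.1768 = 0.35 SD. The resulting shift is r × 0.35 for follow-up values and (r−1) × 0.35 for change scores:

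| r | Follow-up shift (SD) | Share of 0.5 SD | Change-score shift (SD) |
|---|---|---|---|
| 0.3 | 0.10 | 21% | −0.24 |
| 0.5 | 0.17 | 35% | −0.17 |
| 0.7 | 0.24 | 49% | −0.10 |

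**4. Simulation of the rule.** 64 per arm, no clustering, 6,000 runs per setting. The conditional rule uses the follow-up value and adjusts for baseline only if the baseline p<0.05:

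| r | Power, conditional rule | Power, always adjusted | Type I error, conditional rule |
|---|---|---|---|
| 0.3 | 80% | 83% | 5.2% |
| 0.5 | 81% | 90% | 4.4% |
| 0.7 | 83% | 97% | 3.7% |

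**5. How often a gap arises.** The SD of the baseline arm difference is √[(2/64)(1 + 15 × ICC)]. This is 0.177 at ICC 0 and 0.234 at ICC 0.05. The probability of a gap above 0.25 SD is then 16% and 29%.

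**6. Screening many characteristics.** If 10 to 15 independent characteristics are each tested at 5%, at least one is flagged by chance with probability 1−0.95¹⁰ = 40% to 1−0.95¹⁵ = 54%.

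**7. Need for a small-sample correction.** Two arms of four centres leave 8−2 = 6 degrees of freedom at centre level. Testing against 1.96 then gives P(|t₆|>1.96), about 10% instead of 5%.

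**The case against.** **An analysis plan may settle it, and an article condenses.** The article does not merely stay silent; it states a conditional rule. An analysis plan that fixed the covariates in advance would contradict that sentence, so the sentence needs correcting.

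**Baseline may already be used.** The outcome is called change, so baseline may be subtracted, and the analysis sentence also mentions repeated measures. Neither settles the matter. Subtraction is not covariate adjustment, and the repeated-measures wording is attached to differences in proportions. Nor does the section say that the tests are run on change scores, which is why both cases are shown above.

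**Type I error.** A reader might infer that choosing covariates from the data inflates the false-positive rate. For baseline alone under one fixed rule, the simulation shows no meaningful inflation (5.2% to 3.7%). Free choice under an undefined criterion is a plausible further risk, but it has not been quantified.

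**Centres.** A reader might infer that the adjusted regression ignores centres. The text does not say so. It offers a centre random effect in the preceding sentence, on a condition, and does not say whether the two are combined.

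**Size of the gain.** This objection stands in part. The correlations are assumed, and the variance figures are at individual level. Restricting entry to inactive patients may narrow the baseline spread, lower the correlation and make the variances unequal. The gain in between-centre variance was not computed.

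**Conclusion.** The point holds as a matter of precision, conditional bias and pre-specification. The article ties adjustment to observed differences, and no section fixes baseline GPAQ MET-min/week as a covariate.

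At r = 0.3 to 0.6 with equal variances, always adjusting would cut individual-level variance by 35% to 20% against change scores, or by 9% to 36% against follow-up values. Under a p<0.05 reading, a gap of up to 0.35 SD would stay unadjusted. At r = 0.5 that gap moves the estimate by about 0.17 SD, roughly a third of a 0.5 SD effect.

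Two stronger readings are not supported. The first is that chance imbalance is likely: a gap above 0.25 SD has probability 16% to 29%, so it is a real possibility and no more. The second is that the unadjusted test is the declared headline result: the section calls it initial and does not say which result prevails if the unadjusted and adjusted ones differ.

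Confidence is high that the rule should change. The size of the gain is less certain because r, the SD and the ICC are not given.

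**What to change.** - In the main comparison at each follow-up, always include baseline GPAQ MET-min/week as a covariate, on the same transformation as the outcome. Fix that transformation in advance, since the section now leaves the choice between parametric and nonparametric tests to the data.
- Fit this in a model that accounts for health centre whatever the observed centre differences, with a small-sample correction for 8 centres: for example Kenward-Roger, or a cluster-level analysis on about 6 degrees of freedom.
- Treat each secondary outcome likewise, with its own baseline value.
- Use the balance table for description only. Label any adjustment prompted by an observed imbalance as a sensitivity analysis.

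The cost is a change of analysis wording. Table 1 already schedules baseline GPAQ in both arms, so no new data are needed.

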## Discussion/rationale for current trial

Adults with T2D are known to have multiple comorbidities and are generally less active than the general population [23]. Behaviour change programmes targeting vulnerable populations are more effective than those targeting the population at large [24]. Additionally, use of technology namely phone applications (WhatsApp in this study) is a positive followup and monitoring tool to promote longterm PA [15].

PA on a regular basis improves metabolic, blood lipid profile control and quality of life [7]. Additionally, several studies have shown preventive effects of physical activity in individuals with T2D in lowering the risk of cardiovascular disease and premature death [25].

One advantage of the primary care setting in this study is its familiarity to potential participants. More importantly, when interventions are delivered in a clinical setting, desired outcomes are enhanced because of better medical endorsement and feelings of the intervention being an integrated part of care [26].

It is hoped that results from this study will enhance the evidence base for effective routes to increasing physical activity in inactive aduts with T2D; by assessing the impact of MOVEdiabetes intervention on PA levels; providing a platform (feasibility evidence) for the MOVEdiabetes intervention to be initiated in routine primary care clinics; increase understanding of participant engagement, barriers, opportunities; and examining cost related issues about intervention procedures in this clinical and cultural setting.

This study is of direct relevance to the ministry of health of Oman and has the potential to significantly enhance current government action on promoting physical activity. The study will equally assist in formulation and implementation of suitable plans of the National Health Policy Priorities: “5. To promote the health awareness of the community and establish a culture of healthy lifestyles” [27].

## Conclusion

It is hoped that this research will help to inform current policies and practices of the Omani Ministry of Health for the use of a culturally acceptable physical activity interventions as an integral part of care for clients with T2D within the primary health care setting.

## Abbreviations

BMI: Body Mass Index
CHC: Comparison Health Centre
GCC: Gulf Cooperation Council
GPAQ: Global Physical Activity Questionnaire
HbA1c: Glycated heamoglobin
IDF: International Diabetes Federation
IHC: Intervention health centre
IPAQ: International Physical Activity Questionnaire
MENA: Middle East and North Africa
PA: Physical activity
Scot-PASQ: Scottish Physical Activity Screening Questionnaire
WHO: World Health Organization
